## Abstract

For high-risk spinal surgeries, intraoperative neurophysiological monitoring (IONM) is used to detect and prevent intraoperative neurological injury. The motor tracts are monitored by recording and analyzing muscle transcranial electrical stimulation motor evoked potentials (mTc-MEPs). A mTc-MEP amplitude decrease of 50–80% is the most common warning criterion for possible neurological injury. However, these warning criteria often result in false positive warnings. False positives may be caused by inadequate depth of anesthesia and blood pressure on mTc-MEP amplitudes. The aim of this paper is to validate the study protocol in which the goal is to investigate the effects of depth of anesthesia (part 1) and blood pressure (part 2) on mTc-MEPs. Per part, 25 patients will be included. In order to investigate the effects of depth of anesthesia, a processed electroencephalogram (pEEG) monitor will be used. At pEEG values of 30, 40 and 50, mTc-MEP measurements will be performed. To examine the effect of blood pressure on mTc-MEPs the mean arterial pressure will be elevated from 60 to 100 mmHg during which mTc-MEP measurements will be performed. We hypothesize that by understanding the effects of depth of anesthesia and blood pressure on mTc-MEPs, the mTc-MEP monitoring can be interpreted more reliably. This may contribute to fewer false positive warnings. By performing this study after induction and prior to incision, this protocol provides a unique opportunity to study the effects of depths of anesthesia and blood pressure on mTc-MEPs alone with as little confounders as possible.

**Trial registration number** NL7772.

## Background

For complex and high risk spinal surgeries, intraoperative neurophysiological monitoring (IONM) is used, with the aim of detecting and preventing intraoperative neurological injury [1]. For monitoring in spinal surgery, it is advised to monitor both sensory tracts, using somatosensory evoked potentials (SSEPs), and motor tracts, using muscle recorded transcranial electrical stimulation motor evoked potentials, mTc-MEPs [1–4].

The most common warning criterion for possible surgically induced structural neurological injury, is an mTc-MEP amplitude decrease of 50–80% from the baseline value [2, 4–8]. Therefore, an mTc-MEP amplitude decrease of 50–80% warrants immediate exploration of possible causal factors. However, these warning criteria often result in false positive warnings [2]. This can be due to technical issues, but also other factors may influence mTc-MEP amplitudes, including direct effects of anesthetic drugs on neuronal transmission, as well as indirect effects of blood pressure, blood oxygen levels and body temperature resulting in false positive decreases in mTc-MEPs [9–15]. In clinical practice, decreasing the concentration of intravenous anesthetic drugs and elevating blood pressure often help to restore the mTc-MEP amplitude.

It is known that for optimal recording of mTc-MEPs, total intravenous anesthesia (i.e. induction and maintenance of general anesthesia with intravenous infusions of propofol and an opioid) provides more reliable mTc-MEPs than volatile anesthesia (maintenance of anesthesia by administration of a volatile drug through the anesthetic breathing circuit) [16]. However, mTc-MEPs are still very sensitive to the suppressive effects of propofol anesthesia [10, 16–19]. Given the intra- and inter-individual variability in the relationship between blood and effect-site propofol concentrations, and actual clinical effect, it is scientifically important to study the relationship between depth of anesthesia (actual clinical effect) and mTc-MEP characteristics.

Currently, in clinical practice, depth of anesthesia is often objectively assessed by the use of processed electroencephalogram (pEEG) monitors [20]. pEEG monitors acquire the EEG signal recorded by electrodes placed on the forehead (and thus reflecting the electrical activity of the frontal lobe), and use a mathematical algorithm to analyze this signal and generate output [20]. For most pEEG systems, the output is indexed to a range of values from 0 to 100, where 0 indicates no detectable cortical electrical activity (i.e. maximum drug effect) and where 100 indicates a completely conscious patient (i.e. no drug effect measurable) [20]. For optimal anesthesia depth it is recommended that to maintain pEEG values between 40 and 60 [21].

It could be argued that a conventional IONM EEG montage would provide you with even more information about the depth of anesthesia and its effects on mTc-MEP monitoring. In this study protocol we deliberately choose to measure depth of anesthesia with a pEEG monitor instead of a conventional IONM EEG montage, as this is strongly recommended by international guidelines [22]. Even though there is some debate concerning the usefulness (validity) of depth of anaesthesia monitoring in detecting and preventing awareness, their role in hypnotic drug effect titration is well established [23, 24]. In this study, our goal is to standardize the intraoperative hypnotic drug effect. The only validated and clinically convenient way to achieve this is by using a widely available pEEG monitor.(e.g. BIS, entropy or qCON monitor) [25]. Even though a IONM EEG montage would add some useful information, there is currently no known method of using this information to guide anesthetic drug titration.

Another major factor influencing mTc-MEP is cerebral and spinal cord perfusion [26, 27]. Perfusion of any tissue is influenced by vascular resistance and blood pressure. At present there are no clinically available methods to directly assess cerebral and spinal cord perfusion. Indeed, besides global measurements of cardiac output, there are no clinically available methods of directly monitoring perfusion of any tissue. Instead, in clinical practice anesthesiologists use blood pressure measurements as an indirect surrogate of perfusion. Hypotension can occur after induction of anesthesia. It is generally recommended that hypotension should be managed by a combination of optimizing hypnotic and analgesic drug dose, and by optimizing intravascular volume status and vascular tone. The latter is done by administration of fluids and vasopressors such as noradrenaline. Noradrenaline increases blood pressure, but also increases vascular resistance and therefore might even decrease tissue perfusion [10, 28, 29]. It is currently unknown what the exact effects of vasopressor-induced elevation of blood pressure is on mTc-MEPs in humans.

We hypothesize that by understanding the effects of depth of anesthesia and blood pressure on mTc-MEPs, the mTc-MEP monitoring can be interpreted more reliably, resulting in fewer false positive findings. Therefore, the aim of this study protocol is to investigate the effects of depth of anesthesia and blood pressure on mTc-MEPs.

In addition to depth of anesthesia and blood pressure, mTc-MEP measurements are also influenced by other parameters including blood loss, pain and manipulation/movements of the patient. Therefore, in order to investigate the effects of different depths of anesthesia, defined by pEEG, and different blood pressures, defined by the mean arterial pressure (MAP), on mTc-MEP measurements with as few as possible confounding parameters, it should be investigated after anesthetic induction and before surgical incision.

The goal of this paper is to validate this study protocol. In a review by Dwan et al. it was shown that after comparing study protocols with the published results, discrepancies were often found in which at least one primary outcome was changed, introduced or omitted in 50% [30]. Moreover, statistically significant and positive outcomes are more likely to be published, introducing publication bias [31, 32]. Publishing research protocols therefore reduces publication bias, prevents selective publication and increases the transparency of research.

We think that, especially in the field of IONM, the research quality of studies has to be raised to a higher level. By publishing this study protocol we aim to contribute to this.

## Methods/design

### Study design

This research protocol describes two prospective observational studies that will be performed in two parts, in patients that undergo spinal surgery with mTc-MEP monitoring. Study measurements will be performed after anesthetic induction and prior to the surgical incision. In part 1 we will examine the effects of depth of anesthesia, quantified by pEEG, on mTc-MEP characteristics. In part 2 we will examine the effects of blood pressure and noradrenaline induced increases in blood pressure, on mTc-MEP characteristics.

Patients will either participate in part 1 or part 2.

### Study setting

This study will involve patients undergoing spinal surgery with IONM. Eligible patients will be informed about one of the two prospective observational studies at the outpatient clinics or per mail. The studies will be performed at the University Medical Center Groningen at the Neurosurgery, Neurology, Anesthesiology and Orthopedic Departments.

### Inclusion criteria

In order to be eligible to participate in this study, patients must meet all of the following criteria:

≥ 12 years.Demonstrated spinal pathology for which surgery with the use of mTc-MEP monitoring has been planned.Signed and dated informed consent document prior to any study-related procedures.

### Exclusion criteria

A potential subject who meets any of the following criteria will be excluded from participation in this study:

Patient refusal.Existing motor weakness in the left or right tibialis anterior, gastrocnemius, or abductor hallucis muscles.History of epilepsy.Contra-indications to IONM such as presence of a pacemaker or implantable cardioverter-defribillator.Patients with history of stroke or cranial lesions, increased intracranial pressure, heart failure and long-standing hypertension.

### Study objectives and hypotheses

#### Part 1: depth of anesthesia

##### Primary objective

To determine the effect of depth of anesthesia, quantified by pEEG, on the characteristics of mTc-MEP measurements in spinal surgery.

###### Hypothesis

Lighter depth of anesthesia, defined by higher values of pEEG will:

Reduce the threshold voltage required to evoke an mTc-MEP.Increase the mTc-MEP amplitude and the mTc-MEP area under the curve (AUC).

##### Secondary objective 1

To determine if a combination of pEEG and propofol concentration (estimated effect-site concentration and measured plasma concentrations) and/or actual MAP during mTc-MEP registrations, better enable prediction of mTc-MEP characteristics than pEEG alone.

###### Hypothesis

pEEG values alone enable better prediction of mTc-MEP characteristics than propofol concentrations alone..pEEG alone is as good as a more complex model involving pEEG, propofol concentrations and MAP, at enabling prediction of mTc-MEP characteristics.

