##### Hypothesis

Within the specified range of pEEG (40–60), MAP has a greater effect on mTc-MEP characteristics than depth of anesthesia (pEEG).MAP is as good as a more complex model involving MAP, propofol concentrations and pEEG, at predicting mTc-MEP characteristics.

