### Statistical methods

For the statistical analyses of both the primary and secondary outcomes, a linear mixed effects model will be used to account for the repeated mTc-MEP measurements. Below, per outcome and per part of the study, the linear mixed effects models will be more precisely specified.

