#### Part 1: pEEG

##### Primary outcome

For the primary outcome of part 1, a linear mixed effects model will be fitted in which pEEG target (categorical variable with values 30, 40 or 50) will be included as a fixed effect and a random intercept will be used to account for the between-subject variability in the mTc-MEP measurements. Independent normal distributions with mean zero and constant variance will be used to represent the within-subject errors.

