##### Secondary outcome

For the secondary outcome, additional terms for MAP and propofol concentrations (effects site and blood concentration) will be added to the fixed effects structure of the model specified for the primary outcome. The specification of the random effects structure and the residual covariance structure will not change,

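### Part 1 plans no propofol-only model to set against pEEG, and in both parts adding terms to the primary model cannot by itself support an 'as good as' hypothesis

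*Protocol article*

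**What the plan says.** **Part 1.** Secondary objective 1 asks whether pEEG combined with propofol concentration and/or MAP would "better enable prediction of mTc-MEP characteristics than pEEG alone". Two hypotheses follow. The first is that "pEEG values alone enable better prediction of mTc-MEP characteristics than propofol concentrations alone". The second is that "pEEG alone is as good as a more complex model involving pEEG, propofol concentrations and MAP, at enabling prediction of mTc-MEP characteristics".

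**Part 2.** Secondary objective 1 asks the matching question for MAP. Its hypotheses are that MAP has a larger effect than pEEG within the specified pEEG range, and that "MAP is as good as a more complex model involving MAP, propofol concentrations and pEEG, at predicting mTc-MEP characteristics".

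**Statistical methods.** The section announces that, per outcome and per part, "the linear mixed effects models will be more precisely specified". For the Part 1 primary outcome, "pEEG target (categorical variable with values 30, 40 or 50) will be included as a fixed effect", with a random intercept. For the Part 1 secondary outcome, terms for MAP and for effect-site and blood propofol "will be added to the fixed effects structure of the model specified for the primary outcome". Part 2 does the same from the MAP model, adding pEEG and the two propofol measures. The random-effects and residual structures stay as they were. The section names no measure of prediction, rule for comparing models, significance level or margin for these hypotheses.

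**Sample size calculation.** Each part has 25 patients, a number chosen pragmatically, and each is described as hypothesis-generating.

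**The concern.** The secondary hypotheses make two kinds of claim that the listed models do not deliver.

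The first is a contest between two single predictors, pEEG and propofol. Neither model is contained in the other, so both must be fitted and compared. Every Part 1 model listed contains pEEG.

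The second is a claim that a small model predicts as well as a larger one. Adding terms can show that the larger model is better. If it shows nothing, that may be because the added terms are useless or because 25 patients carry too little information to tell. The listed step does not separate the two.

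At stake is the wording of the secondary conclusions. A statement that pEEG or MAP alone suffices would bear on which quantities are followed when mTc-MEPs are interpreted, which is the article's stated purpose. Without a stated comparison, the basis for that statement would be chosen after the data are seen.

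**Working it through.** The article gives no figure to reproduce here, so the main check sets the hypotheses beside the models.

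| Statement | Models needed | Models listed | Addressed? |
|---|---|---|---|
| Part 1 objective: does the combination predict better than pEEG? | pEEG; pEEG + others | both | yes, nested |
| Part 1 hypothesis: pEEG better than propofol | pEEG; propofol | pEEG only | no |
| Part 1 hypothesis: pEEG as good as the full model | pEEG; full; a measure and a margin | both models | only in part |
| Part 2 objective: does the combination predict better than MAP? | MAP; MAP + others | both | yes, nested |
| Part 2 hypothesis: MAP effect larger than pEEG effect | a model with both | extended model | no missing fit |
| Part 2 hypothesis: MAP as good as the full model | MAP; full; a measure and a margin | both models | only in part |

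**Rows available.** In Part 1 the three recordings per pEEG level are averaged and one blood sample follows each series. That gives 25 × 3 = 75 rows with all predictors present. In Part 2 mTc-MEPs are recorded every 2 min over a rise in MAP of about 30 min, so 30 / 2 = about 15 recordings per patient. Blood is drawn only at about 60, 80 and 100 mmHg, so 3 per patient. Once the blood term enters, the extended model rests on about 3 of 15 recordings unless plasma values are carried or interpolated. A comparison with a MAP model fitted to all recordings would compare different data.

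**Why finding no benefit is not equality (illustration only).** Assume a within-patient F test of the added terms in Part 1 at a 5% level; the article states neither.
- Degrees of freedom after patient and level effects: 25 × 3 − 25 − 2 = 48.
- With q = 3 added terms, the denominator has 48 − 3 = 45.
- Noncentrality: λ = 48 × R²/(1 − R²), where R² is the true partial R² of the added terms.

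| R² | λ | power |
|---|---|---|
| 0.05 | 2.53 | 22% |
| 0.10 | 5.33 | 43% |
| 0.15 | 8.47 | 64% |
| 0.20 | 12.0 | 80% |

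Under these assumptions, a true gain of R² = 0.10 would go undetected in 57% of trials. The planned random-intercept model also uses differences between patients, which this test discards, so these are not the plan's own operating characteristics.

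**Why no size can be given.** In simulations of the same within-patient test, with effect-site concentration and MAP added, propofol was made the only true driver. The assumed slope was 0.3 to 0.8 residual SD per step in concentration between adjacent pEEG levels, and the scatter within a level was 0.3 to 0.8 steps. The added terms were non-significant in 4% to 92% of runs. In 3% to 64% of runs they were non-significant although a propofol-only model had the lower AIC. The width of these ranges comes from the assumptions, and the article supplies nothing to narrow them. What they do show is that the extended model can look unhelpful while propofol alone is the better-fitting predictor, and that only a separate propofol-only fit reveals it.

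**The case against.** The case on the other side is substantial.

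- **The objectives are answerable.** They ask whether a combination predicts better than pEEG or MAP alone, and the extended models address that. This stands.
- **The measure and margin may sit elsewhere.** A condensed article commonly leaves these to the full protocol or SAP, and fitting the base and extended models is compatible with AIC or cross-validation. This stands in part: their absence alone would not be a finding. It does not cover the Part 1 gap, because the article says it specifies the models for each outcome and part, and the set it gives has no propofol-only model. Nor does it alter the logic that adding terms cannot by itself support 'as good as'.
- **The study is hypothesis-generating.** No primary result and no data collection is affected, and the propofol data are gathered anyway. This stands and limits the severity.

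Three stronger readings are tempting but not supported:

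- A reader might infer that non-significance will be read as equality. The article states no test and no reading rule for these hypotheses.
- A reader might extend the missing propofol-only model to Part 2. Part 2 states no such hypothesis.
- A reader might infer that the added terms are so collinear with pEEG that they will fail whatever the truth. In Part 1 propofol is indeed titrated to the pEEG target, but no correlation is given, and the Discussion stresses marked discrepancy between effect-site concentration and clinical effect. The argument does not carry to Part 2, where noradrenaline moves MAP while propofol is adjusted to hold pEEG in range.

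**Conclusion.** The concern holds in limited form. Followed as written, the Part 1 plan cannot answer whether pEEG alone predicts better than propofol alone, because no listed model leaves pEEG out. In both parts, extending the primary model cannot by itself establish that the simple model is as good. These conclusions follow from the text and need no numerical assumption.

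No magnitude can be given from the document; the figures above illustrate the logic under assumed inputs and are not estimates for this trial. As a secondary matter in a hypothesis-generating study, this is minor to moderate. It governs what may be concluded about the sufficiency of pEEG or MAP, and nothing in the primary analyses.

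**What to change.** 1. **Part 1: add the missing comparators.** Fit propofol-only models, with effect-site and plasma concentration separately, under the same random-intercept structure. Compare each with a pEEG-only model that uses measured pEEG instead of the target category. Table 1 lists pEEG among the values collected after recordings, but the Part 1 text names only effect-site concentration and MAP, so confirm that measured pEEG is stored per recording.
2. **Both parts: use identical rows.** Refit the simple model on the rows that the extended model can use. In Part 2 this means the rows with plasma values for any model containing the blood term; models without it can be compared on all recordings.
3. **Both parts: name one predictive measure**, such as leave-one-patient-out error or AIC from maximum-likelihood fits, and give an interval for the difference. If prediction error is chosen, say whether it concerns a new patient's level or change within a patient.
4. **Wording.** Report the difference and its interval as the estimated added value. Claim 'as good as' only if the interval lies within a margin fixed beforehand; otherwise write that a difference was not shown.

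The cost is a few extra model fits, a sentence or two in the statistical methods, and probably a more cautious secondary conclusion. Provided that measured pEEG is stored, no new data are needed.

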#### Part 2: Blood pressure

##### Primary objective

To determine the effects of increasing the MAP with a vasopressor infusion on the characteristics of mTc-MEP measurements in spinal surgery.

###### Hypothesis

A Higher MAP will:

Reduce the threshold voltage required to evoke an mTc-MEP.Increase the mTc-MEP amplitude and the mTc-MEP AUC.

A range of alternative hypotheses will also be explored. These include:

There is a biphasic relationship between MAP and mTc-MEP amplitude and AUC (with an initial improvement and a subsequent decrease at higher noradrenaline doses and MAP values).The MAP at which optimal mTc-MEP amplitudes and AUCs are found is age-dependent.

#### Secondary objective 1

To determine if a combination of MAP, with pEEG and/or propofol concentration (estimated effect-site concentration, or estimated or measured plasma concentrations) enables better prediction of mTc-MEP characteristics than the MAP on its own.

##### Hypothesis

Within the specified range of pEEG (40–60), MAP has a greater effect on mTc-MEP characteristics than depth of anesthesia (pEEG).MAP is as good as a more complex model involving MAP, propofol concentrations and pEEG, at predicting mTc-MEP characteristics.

### Muscle recorded transcranial electrical stimulation motor evoked potentials

Intraoperative mTc-MEPs will be performed according to a standard procedure using a custom-made constant voltage stimulator (NIM-Eclipse E4 IONM system, Medtronic BV, The Netherlands). Transcranial electrical stimuli will be applied at locations Cpl1–Cpl2 (1 cm posterior and 1 cm lateral to C1 and C2), a modification of the international 10–20 system. Muscle motor evoked potentials will be recorded using surface electrodes (3M® ECG) on at least the left and right tibialis anterior (TA), the left and right gastrocnemius (GAS) and the left and right abductor hallucis (AH) muscles.

For each muscle recording site, an mTc-MEP threshold will be determined. The mTc-MEP threshold is defined as the voltage required to obtain an amplitude of at least 50 µV. Besides this, stimulation settings will be optimized to achieve supramaximal stimulation. A pulse train will consist of 5 square wave stimuli with either a pulse duration of 0.075 ms with an inter stimulus interval (ISI) of 1.5 ms or a pulse duration of 0.300 ms with an ISI of 3 ms. Depending on the height of amplitude and the amount of muscles that will be elicitable one of these two settings is chosen. If the pulse duration of 0.075 ms will be chosen the ISI will be optimized as well, ranging from 1 to 4 ms.

